## Abstract

**Background:**

Deaf American Sign Language (ASL) users often struggle with limited health literacy compared with their hearing peers. However, the mechanisms driving limited health literacy and how this may impact access to and understanding of health information for Deaf individuals have not been determined. Deaf individuals are more likely than hearing individuals to use the internet, yet they continue to report significant barriers to health information. This study presents an opportunity to identify key targets that impact information access for a largely marginalized population.

**Objective:**

This study aims to elucidate the role of information marginalization on health literacy in Deaf ASL users and to better understand the mechanisms of health literacy in this population for the purpose of identifying viable targets for future health literacy interventions.

**Methods:**

This is an exploratory mixed methods study to identify predictors and moderators of health literacy in the Deaf population. These predictors of health literacy will be used to inform the second step that qualitatively explains the findings, including how Deaf individuals access and understand Web-based health information. Multiple interviewer- and computer-based instruments underwent translation and adaptation, from English to ASL, to make them accessible for the Deaf participants in our study. A planned sample of 450 Deaf ASL users and 450 hearing native English speakers, aged 18 to 70 years, will be recruited from 3 partnering sites: Rochester, NY; Flint, MI; and Chicago, IL. These individuals will participate in a single data collection visit. A subset of participants (approximately 30) with key characteristics of interest will be invited for a second data collection visit to observe and inquire more about their ability to directly access, navigate, and comprehend Web-based health information. The study will help assess how the ways health literacy and information are visualized may differ between Deaf individuals and hearing individuals. The study will also survey participants’ ownership and use of computer and mobile devices and their level of Web-based information use, including health information.

**Results:**

Adaptation and translation of protocols and instruments have been completed and are now in use for the study. Recruitment is underway and will continue until late 2020. Results from this study will be used to provide a guide on how to structure Web-based health information in a way that maximizes accessibility and improves health literacy for Deaf individuals.

**Conclusions:**

The results from this mixed methods proposal will advance what is known about health literacy and health information accessibility for Deaf individuals. This innovative study will generate rich data on how to formulate health information and health literacy interventions more accurately to take advantage of visual learning skills.

**International Registered Report Identifier (IRRID):**

PRR1-10.2196/14889

## Introduction

### Background

Deaf American Sign Language (ASL) users are nearly 7 times more likely than their hearing peers to have inadequate health literacy [1]. Deaf ASL users (henceforth, Deaf) rarely receive language concordant health care services and are at highest risk for miscommunication with their health care providers. Deaf individuals understand less than 30% of what is being said through lipreading [2,3]. Furthermore, prose literacy poses a challenge for Deaf individuals; the average Deaf individual reads English at the fifth- to sixth-grade level [1,4-7]. The use of interpreters is the standard of care for Deaf ASL users, yet they are infrequently provided [8]. The majority of Deaf individuals (approximately 95%) have hearing family members who do not sign. Thus, many experience the *dinner table* syndrome, where they have encountered years at the dinner table watching close family members and friends converse with each other while being unable to understand what is being said, depriving them of incidental learning opportunities that many hearing individuals take for granted [9]. The loss of incidental learning opportunities and information marginalization for Deaf individuals occurs daily in a broad range of work, schools, friends, families, government, media, and health care contexts [1]. Many Deaf ASL users learn language, health information, and even culture via peers rather than family [10] and struggle to identify and correct misinformation [11]. Due to this communication-depleted milieu, inadequate health literacy may be an important cause of the lower level of health-related knowledge and worse health outcomes that have been observed among Deaf individuals.

Deaf individuals, because of their social and language marginalization, appear to use Web-based health information more frequently than the general population [12,13]. However, it is unclear if Deaf individuals access Web-based health information or other information sources effectively and what degree of impact this may have on their health literacy. In the general population, there is evidence that health literacy impacts mortality, yet the connection remains inconsistent when looking at other clinical outcomes [14]. In multiple studies, positive associations with both health literacy and electronic health (eHealth) literacy and improved quality of life, better use of health care services, and improved health behaviors among individuals with different types of health conditions were demonstrated [15-17]. An area of concern is that disadvantaged populations, notably those with chronic health conditions or disabilities, may struggle with eHealth literacy. This may promote additional inequalities in their ability for Web-based health information to influence positive outcomes such as self-management of health care needs in these individuals. What is needed is to understand how to design technology and Web-based health information in a way that may benefit these types of consumers [18,19]. As Deaf individuals communicate through a visual language, the proposed study provides an opportunity to determine optimal visual-based information sources, providing another avenue to help those with lower health literacy. Individuals with low health literacy struggle in locating relevant Web-based health information and may fixate on irrelevant aspects of displayed information [20]. Such a phenomenon may be important for populations such as the Deaf who are dependent on visual mechanisms for communication and for overcoming information gaps.

This study describes the methods used to study the role of information marginalization on health literacy for Deaf individuals. The authors describe approaches for instrument adaptations and measures applicable for Deaf individuals who use ASL. Finally, a description of the unique aspects of our proposed data collection method is shared in this paper. The research objectives are two-fold: (1) to elucidate the role of information marginalization on health literacy in Deaf signers and (2) to better understand the mechanisms of health literacy in this population for the purpose of identifying viable targets for future health literacy intervention development.

### Study’s Theoretical Framework

There are few mechanism-based studies in health literacy research and none involving Deaf and hard of hearing individuals. A review of the literature helped with developing ideal conceptual models to guide the project’s proposal. The authors modified and created a hybrid of 3 widely used health literacy and diffusion theory conceptual models: (1) the attitudes, skills, and knowledge (ASK) model [21], (2) the health literacy model [22], and (3) the diffusion theory [23] for Deaf individuals. Figure 1 illustrates constructs that are relevant to health literacy and health-related information. Sociodemographics, cognition, educational achievement including reading skills and task performances, and general health knowledge have all been shown to be related to each other with respect to health literacy in the general population [21]. Additional aspects of health literacy that need to be better understood in the Deaf community include the role of attitudes (ie, the feeling and trust one has toward information), skills (ie, the tools that allow one to seek, obtain, and understand information), and knowledge (ie, demonstrates comprehension). It is hypothesized that the factors outlined in the model are key elements of health literacy for Deaf individuals. As a result, our Deaf Health Literacy conceptual model regarding information includes 3 main concepts that lead to health outcomes and are being used in this study to inform data collection and analysis.

**Figure figure1:**
[figure not shown]
Deaf health literacy conceptual model for information.

To help explain how and why certain characteristics may impact health literacy, including ability to access, navigate, and understand Web-based health information, a qualitative interview along with thematic analysis will be performed. This will explain the interrelation in outcomes of interest (eg, what characteristics are associated with adequate health literacy), intermediary outcomes (eg, what backgrounds, skills, and contextual factors allow for better navigational ability on the Web), and personal conditions that need to be explored further (eg, cognitive issues).

## Methods

### Overview

For this study, there are 3 proposed aims. Aim 1 is to evaluate differences in ASK, regarding health information for both Deaf signers and hearing English speakers. Aim 2 plans to assess hearing status as an effect modifier of the association between health literacy and ASK with health information. Aim 3 will qualitatively assess the impact of health information accessibility and patterns of use on health literacy with one-on-one elicitation interviews. This will be based on actual Web-based health information searches for 4 clinical vignettes using an observed task fulfillment experiment as a prompt. The goal of this aim is to explore differences with Web-based health information search ability and health knowledge acquisition in a subsample of Deaf and hearing individuals recruited from aims 1 and 2. The University of Michigan institutional review board (IRB) approved the study and provides coordination with the following IRBs: Sinai Hospital, Rochester Insitute of Technology, and Hurley Medical Center (HMC). The study is also registered at the ClinicalTrials.gov under ID NCT03093779.

### Study Design

The study uses an explanatory sequential mixed methods design [24] with extensive quantitative data collection procedures to identify predictors and moderators of health literacy. We will first conduct a cross-sectional study to collect predictors of health literacy. These predictors of health literacy will be used to inform the subsequent phase of qualitative assessment. For example, elicitation interviews with selected participants returning for the second data collection visit will be used to help explain the quantitative results and to help elucidate how Deaf individuals access and understand Web-based health information. The study will use a stratified sampling approach to invite participants of certain characteristics to return for further data collection. Characteristics of interest will be based on quantitative analyses that show significant associations between health literacy and any of the measured variables (eg, educational attainment, age, or reading literacy). Approximately 15 Deaf and 15 hearing participants with inadequate health literacy and another 15 Deaf and 15 hearing participants with adequate health literacy will return for a second visit to conduct a task performance on a desktop computer and participate in a follow-up interview designed to learn more about their decision making and preferences. The return visit will involve a qualitative assessment using elicitation interviews to help explain any of the quantitative results. The goal is to learn how and why Deaf individuals access and understand health information (Figure 2) and how this may differ from hearing individuals.

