### Study Setting and Participants

The study will recruit 450 Deaf and 450 hearing participants at 3 primary data collection sites. The sites include HMC at Flint, MI (selected because of its diverse Deaf patient population, along with previous research collaborations with the University of Michigan); The National Technical Institute of the Deaf (NTID), which is housed at the Rochester Institute of Technology in Rochester, NY (selected because of NTID’s experience in research and Rochester’s highly educated Deaf community); and The Sinai Deaf Health program in Chicago, IL (selected because of its long-standing commitment to Deaf health education and research and its minority community).

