Building on the methodology used in previous Web-based search behavior studies [46], participants’ search skills and success in addressing the clinical scenario tasks will be assessed using a combination of methods. First, based on the browser log and interaction data gathered by the usability software, we will compute summary statistics, such as the total time (in minutes) spent in searching, the number of unique websites and pages visited, and the number and characteristics of queries issued, involved in completing each task. Second, we will include time-based retrieval measures [47] that can characterize and quantify how a participant’s search progress evolves over time. Knowledge acquisition will be measured by the number of correct responses based on the clinical vignettes (score range between 0 and 12). All measures representing navigation skill and knowledge acquisition will be compared across levels of health literacy (adequate vs intermediate/inadequate) on the subgroup of the preselected 30 Deaf participants using 2 sample *t* tests. Although it is anticipated that power will be low to observe statistical significance, the primary objective for this comparison is to identify trends. Search progress for the clinical scenarios will be defined in terms of the quality of health information pages found during the search task. To assess the quality of health information pages, the research team will evaluate the Web pages/resources returned by participant searches or visited by the participant via browser navigation in terms of accuracy and coverage of the target facts in the reference set. Any differences will be discussed until a consensus is obtained.

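### The Aim 3 literacy comparison uses plain t tests with no stated balance or adjustment for site, so its trends are left open to confounding by site

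*Protocol article*

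**What the plan says.** Study Design sets the Aim 3 sample as two literacy groups. The inadequate group has about 15 people of each hearing status. For the adequate group the text reads: "another 15 Deaf and 15 hearing participants with adequate health literacy will return for a second visit". On how people are chosen within those cells it says "The study will use a stratified sampling approach to invite participants of certain characteristics to return for further data collection", and adds: "Characteristics of interest will be based on quantitative analyses that show significant associations between health literacy and any of the measured variables". Education, age and reading literacy are its examples. Site is neither named as a stratum nor ruled out.

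Analyses for Aim 3 says the navigation and knowledge measures "will be compared across levels of health literacy (adequate vs intermediate/inadequate) on the subgroup of the preselected 30 Deaf participants using 2 sample" t tests. No covariate or site term is given. The same section expects low power and says the purpose is to look for trends.

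Site is handled differently elsewhere. Statistical Analyses for Aim 1 controls for variability across sites in the model. Statistical Analyses for Aim 2 adjusts the partial correlations, and the supporting regression, for site.

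Study Setting and Participants gives the reasons for choosing each site. Flint was "selected because of its diverse Deaf patient population", among other reasons. Rochester was "selected because of NTID’s experience in research and Rochester’s highly educated Deaf community". Chicago was chosen for its commitment to Deaf health education and research and for its minority community.

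**The concern.** The plan treats site as something to control for in Aims 1 and 2. It then drops that control in Aim 3, which draws on the same participants and sites. If the adequate and inadequate Deaf cells end up with different site mixes, a difference in search time, pages visited or vignette score could come partly from site, meaning the local community, the setting, and the interviewer if interviewers differ by site.

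This matters because Table 2 asks Aim 3 whether Deaf individuals' health literacy determines the quality of navigation and comprehension, and because Aim 3 is meant to explain the results of Aims 1 and 2. The interviews are read across the same literacy strata, and a theme cannot be adjusted for site by regression afterwards.

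**Working it through.** The plan has no figure to reproduce here: the cell size of 15 is not derived, and neither site mix nor site effect is given. The check is a sensitivity calculation on stated assumptions.

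**Inputs from the article.** 15 adequate and 15 inadequate Deaf returnees (Study Design), which matches the 30 Deaf participants in Analyses for Aim 3; three sites; an unadjusted two-sample t test.

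**Assumptions.** No true literacy effect. One site's outcomes are shifted by e = 0.3 to 0.8 SD. The within-site SD is 1. The mixes below list the shifted site first, adequate cell versus inadequate cell.

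**Formulas**
- Bias of the unadjusted difference = (a − i)/15 × e, where a and i are the shifted site's counts in the two cells.
- Unadjusted standard error = √(2/15) = 0.365 SD.
- Standard error with site in the model = 1/√Σ[aₛiₛ/(aₛ+iₛ)], summed over the three sites.

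| Site mix | Bias, e = 0.3 to 0.8 | Sum for adjusted SE | Adjusted SE |
|---|---|---|---|
| Equal, 5/5/5 v 5/5/5 | 0 | 2.5+2.5+2.5 = 7.5 | 0.365 |
| Mild, 7/4/4 v 3/6/6 | 4/15 × e = 0.08 to 0.21 | 2.1+2.4+2.4 = 6.9 | 0.381 |
| Moderate, 9/3/3 v 3/6/6 | 6/15 × e = 0.12 to 0.32 | 2.25+2+2 = 6.25 | 0.400 |
| Extreme, 11/2/2 v 1/7/7 | 10/15 × e = 0.20 to 0.53 | 0.917+1.556+1.556 = 4.028 | 0.498 |

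**Simulation** (8,000 runs per case, two-sided 0.05). The plain t test's false-positive rate was 5.5 to 6.8% under mild imbalance, 5.9 to 10.9% under moderate and 8.4 to 25.9% under extreme. With equal mix it was 3.6 to 4.4%. With site in the model, bias was about 0 and the false-positive rate about 5% under every mix.

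**Direction of a trend.** With no literacy effect, the chance that the observed difference points the way site pushes it is Φ(bias/0.365). At e = 0.5 this is Φ(0.133/0.365) = 64% under mild imbalance and Φ(0.20/0.365) = 71% under moderate, instead of 50%.

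**Scale.** At 15 v 15 the smallest effect detectable with 80% power is about 1.06 SD, and power at 0.5 SD is 26%. In most of these cases sampling error exceeds the bias.

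**The case against.** The strongest reply is that nothing shows an imbalance will occur. The article reports no health literacy by site, no returnee counts by site and no site effect on searching. A reader might infer from Rochester's "highly educated Deaf community" that the adequate cell will fill mainly from Rochester and that the comparison therefore is confounded, in a known direction. The documents do not support that. They describe education there, not health literacy. Chicago's commitment to Deaf health education could work the other way. Study Design also allows selection on education, which could remove much of any Rochester difference. This stands, and it limits the point to an open risk of unknown size.

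A reader might also cite the remark on regional signs in Timeline and Challenges. There it describes a check made on the translated instruments, alongside joint staff training, so it is evidence of care. It does not show a site effect. Nothing says that Aim 3 interviewers differ by site.

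Site quotas for an interview subsample may sit in a full protocol that is not shown, so their absence from an article is not in itself an error. That is fair. The point rests on the t test, which the article does state, and on its contrast with Aims 1 and 2.

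Finally, the comparison is declared low-powered and exploratory within a mainly qualitative aim. That lowers the stakes but does not answer the point. The declared output is trends, and a site tilt pushes their direction, whereas random error favours neither.

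**Conclusion.** The point holds as a low-cost improvement to a stated method. The Aim 3 comparison omits the site control used in Aims 1 and 2, and no site balance is stated for selection, so its trends and interview themes are left open to confounding by site. The size is unknown. On the assumed mild-to-moderate mixes and site effects it is about 0.1 to 0.3 SD, below one standard error (0.365 SD).

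It would be wrong to conclude that the quantitative comparison could not be repaired in the analysis: a site term removes the bias under every mix tried, at some cost in precision. That remedy does not extend to the interviews, which is the main reason to act at selection. Nor would site balance make a trend attributable to literacy, since the literacy groups may still differ in education, age or cognition.

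**What to change.** - **Selection.** Balance site across the two literacy cells within each hearing group as far as the pool allows. The target is about 5 per site per cell (3 × 5 = 15). Where a site cannot fill a cell, match its count in the opposite literacy cell.
- **Analysis.** Replace the plain t test with a linear model containing literacy level and site.
- **Reporting.** Give the site mix by cell, and keep the contrast labelled exploratory.

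No additional participants are needed. The article says recruitment is still under way and makes selection wait on the quantitative results, so the rule can be set before returnees are invited.

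The costs are a smaller eligible pool in whichever literacy category is scarcer at a site (the article gives no such counts), possible competition with the other selection characteristics, and 2 degrees of freedom (28 to 26). If balance is not achieved, the standard error rises from 0.365 to between 0.38 and 0.50 SD on the unequal mixes above.

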**Figure figure2:**
[figure not shown]
Overall study design. ASL-NVS: American sign language-newest vital sign.

The project uses a community advisory board (CAB) with representation from study sites. The CAB is designed to provide community oversight and guidance on the research protocol development and interpretation of findings. The board consists of 6 Deaf community members, 2 from each of the research data collection sites.

### Study Setting and Participants

The study will recruit 450 Deaf and 450 hearing participants at 3 primary data collection sites. The sites include HMC at Flint, MI (selected because of its diverse Deaf patient population, along with previous research collaborations with the University of Michigan); The National Technical Institute of the Deaf (NTID), which is housed at the Rochester Institute of Technology in Rochester, NY (selected because of NTID’s experience in research and Rochester’s highly educated Deaf community); and The Sinai Deaf Health program in Chicago, IL (selected because of its long-standing commitment to Deaf health education and research and its minority community).

